## Abstract

**Introduction:**

Pain is a highly prevalent symptom in the hospital setting, but treatment options remain limited. Harnessing the placebo effect in an ethical manner could provide a new possibility to reduce pain in clinical practice. So called open-label placebos (OLP) have been shown to elicit significant effects in reducing acute pain. But, before implementation, more knowledge concerning the properties of OLPs is needed. This study aims to assess the duration of analgesic effects from OLP and to determine the possibility of boosting such effects.

**Methods and analysis:**

This is the protocol of an ongoing (first patient enrolled in March 2023) single-site randomized trial investigating OLPs in two parts (i.e., substudies). In both parts, pain will be induced in healthy adults using an intradermal electrical stimulation model. Participants in Part 1 will have two study visits: An interventional visit with one OLP injection accompanied by an evidence-based treatment rationale and a control visit with no treatment. For Part 2, participants will be randomized into three groups: (1) A fixed-time “Booster” group including one single repetition of the OLP injection at a fixed time point, (2) an on-demand “Booster” group including one single repetition of the OLP injection on-demand, and (3) a control group who will receive just one OLP injection. Differences in pain ratings over time (using the Numeric Rating Scale) will be analyzed with several two-sample *t*-tests. The time point for a fixed-time “Booster” in Part 2 will be derived from Part 1 with additional statistical tools such as a broken-stick mixed-effect model.

**Discussion:**

This study aims to further characterize the analgesic effects of OLPs. In doing so, it will provide valuable information needed for later implementation of OLPs in clinical practice, where they could play a role in multimodal analgesic concepts.

**Ethics and dissemination:**

The “Ethikkommission Nordwest- und Zentralschweiz” (BASEC 2023-00296) approved the study protocol. Results of the analysis will be submitted for publication in a peer-reviewed journal.

**Clinical Trial Registration:**

This study is registered at ClinicalTrials.gov (NCT05819476) and is listed in the Swiss National Registry at kofam.ch (SNCTP000005470).

## 1 Introduction

Pain is highly prevalent in hospital settings, with up to 84% of adult patients reporting it as a symptom and up to 36% describing it as severe (1). Standard systemic treatment for acute pain mainly consists of multimodal analgesic concepts including acetaminophen, metamizol, non-steroidal anti-inflammatory drugs, and opioids (2–7). However, the use of these drugs is often restricted due to contraindications, side-effects, and adverse events (2–8). Therefore, broadly applicable new treatment options with fewer side-effects would be valuable.

The word placebo is used nowadays to describe sham treatments and “inert” substances like sugar pills and saline injections (9–12). Placebos have been proven to elicit clinically significant effects in various conditions, including pain (9–16). Moreover, due to the “inert” nature of placebos, there are few to no contraindications. Side-effects occurring after the administration of placebos, termed the nocebo effect, are rare and usually stem from the expectation of adverse events (11, 17). So, one could argue that placebos themselves are very safe and could be used in most patients. Nevertheless, ethical concerns about the deceptive nature of placebos (18–20) have prevented their implementation in clinical practice.

To address this issue, it might be possible to prescribe placebos openly, without deception. This concept was proposed and found to be effective back in 1965 (21). Over the last two decades, this topic has become an emerging field of research with several studies focusing on these so-called open-label placebos (OLPs) (22–55). Two meta-analyses summarize clinical OLP studies and highlight significant effects in various conditions, such as allergic rhinitis, menopausal hot flushes, attention deficit hyperactivity disorder, cancer-related fatigue, irritable bowel syndrome, and chronic low back pain (56, 57). Findings on acute pain, though limited, are promising (25–29, 32, 35, 49, 55). To our knowledge, the effects of OLPs on acute pain-associated phenomena, hyperalgesia and allodynia, have only been investigated in one study thus far (55).

As mentioned by the Initiative on Methods, Measurement, and Pain Assessment in Clinical Trials (IMMPACT), characterizing the efficacy of a new analgesic is crucial to its development (58). Attributes of efficacy include onset of effect, maximum analgesic effect, duration of analgesia, and overall analgesic effects across the therapeutic dose range of the drug (58). In a proof-of-concept study from our own research group, we were able to show that OLP injections were able to significantly reduce pain (21% reduction), hyperalgesia and allodynia (47% reduction for both) in a population of healthy adult males experiencing induced pain (55). Although onset of OLP analgesia was nearly immediate, duration could not be observed in full as the analgesic effects lasted beyond the entire 70-min measurement period (55). In a study investigating OLP analgesia in migraine attacks, significant reduction of pain could still be measured two hours after intake of OLP pills (49). To our knowledge, observations over the full duration of OLP analgesia and placebo analgesia are absent. Therapeutic dose range of OLPs – although not for acute pain, but for participant well-being – was investigated by El Brihi et al. (31), but they did not find an influence of dose on their outcomes.

Furthermore, IMMPACT emphasizes the need to establish profiles of new analgesic therapies (58) and recommends the use of both single-dose and multiple-dose study designs (58). In using deceptive placebos, multiple placebos and more frequent intake have been shown to increase effects (59, 60). However, there is – to the best of our knowledge – only one study investigating possible superiority of repeated OLP administration over one-time OLP administration (31), showing no statistically significant influence of OLP repetition on participant well-being. Nevertheless, there are several studies administering multiple-dose OLPs in multiple day interventions on various conditions (e.g., 31, 33–39, 42, 43, 45, 46, 48, 51). But, none of these studies investigated whether repeated OLP intake actually is superior to single-dose intake and none did determine the optimal timing of repeat dosing. Likely, the decision to use multiple-dose OLPs (i.e., two OLP pills twice a day in most studies) comes from weighting the evidence on deceptive placebos mentioned above with evidence suggesting that “simple dosing regimens encourage higher adherence and thus larger placebo effects” (31).

This randomized study aims to fill the gaps in characterizing the efficacy of OLPs in acute pain. We will measure subjective pain ratings and areas of hyperalgesia and allodynia in a well-established experimental pain model (61) and investigate analgesia elicited by OLP injections accompanied by a short evidence-based treatment rationale, as in a previous study (55). To achieve this goal, Part 1 of our study will examine the duration of OLP analgesia and reevaluate the onset and size of the effect. Given the “inert” nature of OLPs, we assume that results of El Brihi et al. (31) concerning OLP dose effects on participant well-being will be generalizable to all outcomes and will, therefore, not evaluate different OLP dosages. Nevertheless and as stated above, multiple doses of placebos and more frequent intake increase effects (59, 60). Furthermore, participants given a choice over their (deceptive) placebo treatment experience enhanced placebo effects (62). For example, participants in control of the time point of administration of their placebo treatment experienced more placebo analgesia than participants without this control [(63); please note: this study investigated deceptive placebos and used conditioning effects]. This leads us to Part 2 of our study in which we will compare outcomes between participants receiving one OLP injection, participants receiving one repetition of the injection at a fixed time point, and participants receiving one repetition of the injection on demand (i.e., the last group will choose if and when they would like to receive the placebo “Booster”). This form of multiple-dose study aims to fill knowledge gaps concerning OLPs.

## 2 Methods and analysis

### 2.1 Study objectives

The primary objective of this study is to further investigate the effect of OLP administration on acute pain in an experimental model of acute pain (simulating wound pain).

#### 2.1.1 Part 1

##### 2.1.1.1 Primary objective

We hypothesize that there will be a difference in the overall subjective pain ratings when comparing subjects receiving a single OLP injection with control subjects receiving no treatment, as suggested by a previous study from our group (55).

##### 2.1.1.2 Further objectives

We hypothesize that there will be a difference in the areas of hyperalgesia and allodynia when comparing subjects receiving a single OLP injection with control subjects receiving no treatment. We hypothesize that the expected difference in subjective pain ratings, hyperalgesia, and allodynia will diminish or even disappear over time as a regular end of dose phenomenon. Insight on the timing of when the effect of the placebo decreases will allow us to determine when to administer a second dose (booster) of OLP (fixed-time booster) in Part 2.

#### 2.1.2 Part 2

##### 2.1.2.1 Primary objective

We hypothesize that there will be a difference in overall subjective pain ratings when comparing subjects receiving a repeated (i.e., two OLP injections) vs. a single OLP injection.

##### 2.1.2.2 Further objectives

In addition, we hypothesize that, in comparison to receiving a repeated OLP injection at a fixed time point, overall subjective pain ratings will be different when subjects receive the second application of OLP on-demand. Moreover, we hypothesize that there will be a difference in areas of hyperalgesia and allodynia when comparing subjects receiving a repeated OLP injection (i.e., two OLP injections) with subjects receiving only a single injection of OLP and when comparing subjects receiving the second application at a fixed time point with subjects receiving the second application on demand.

### 2.2 Study design

#### 2.2.1 Part 1

The first part of this study has been designed as a confirmatory, randomized, two-arm, assessor-blinded cross-over trial in a single center setup at the University Hospital of Basel. We will compare the effects of OLP on acute induced pain intra-individually by delivering the study intervention (OLP) as well as the control intervention (no treatment) to every participant and randomizing only for order of intervention. Thus, the participants will act as their own control.

The study design for Part 1 of this study is also shown in Figure 1.

**FIGURE 1 F1:**
[figure not shown]
Study design, part 1.

#### 2.2.2 Part 2

The second part of this study has been designed as a proof-of-concept, randomized, controlled, three-arm trial in a single center setup at the University Hospital of Basel. We will compare the effects of an OLP “Booster” inter-individually by analyzing three groups: A fixed-time “Booster” group (who will receive a first OLP at the beginning of the study visit and a second one at a time point derived from Part 1), an on-demand “Booster” group (who will receive a first OLP at the beginning of the study visit and a second one when participants ask for it), and a control group (who will receive only one OLP at the beginning of the study visit). Due to organizational reasons, blinding of the assessor will not be possible in Part 2.

The study design for Part 2 of this study is also shown in Figure 2.

**FIGURE 2 F2:**
[figure not shown]
Study design, part 2.

### 2.3 Study population

We will include a total of 36 and 105 healthy adults in Part 1 and Part 2 of our study, respectively. Participants will need to meet all of the following inclusion criteria:

•Healthy volunteers (American Society of Anaesthesiologists Class I or II) aged 18–65 years•Body Mass Index between 18 and 25 kg/m^2^•Able to understand the study and the Numeric Rating Scale (NRS)•Able to give informed consent (IC)

The presence of any of the following exclusion criteria will lead to exclusion of the participant:

•Participation in a previous OLP study; for Part 2, this includes Part 1 of this study•Regular intake of medications or drugs potentially interfering with pain sensation (analgesics, opioids, antihistamines, calcium and potassium channel blockers, serotonin/noradrenaline reuptake inhibitors, and corticosteroids)•Neuropathy•Chronic pain•Neuromuscular disease•Dermatological disease (i.e., atopic dermatitis)•Psychiatric disorder•Pregnancy/lactation

### 2.4 Study procedures

#### 2.4.1 Recruitment and screening

Participants will be recruited through advertising on the homepage of the University of Basel. For both parts, more participants will be screened to replace possible drop-outs. A balanced gender distribution will be ensured during recruitment.

The volunteers will be contacted by the study team andreceive oral and written information about the study (Supplementary material). Inclusion and exclusion criteria will be assessed and, if eligibility is given, informed consent will be obtained.

In recognition of their efforts, participants will receive standardized financial compensation (i.e., CHF 240.- for the two visits in Part 1 and CHF 120.- for Part 2, respectively) after completion of their study visits.

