#### 2.4.3 Randomization

As every participant in Part 1 will receive all of the possible treatments, we are only able to randomize the order of the treatments, and thereby control for excitement and habituation effects.

For Part 2, group allocation will be randomized (control group, fixed-time “Booster” group, on-demand “Booster” group).

Randomization will be performed by study staff not involved in study assessments using a random number generator.^1^

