### 2.8 Sample size

For Part 1, we estimated how many participants are needed to achieve an 80% power to detect a difference of 45 in the AUPC between the interventional visit and the control visit. Based on data from our previous study (55), we assumed a standard deviation of 67 for the differences in the AUPC. The assumed difference and standard deviation of the difference correspond to a Cohen’s d of 0.7. Calculations were done assuming a two-sided alpha of 5% and using a two-sample *t*-test for comparison. The number of participants needed for Part 1 is 36.

The sample size for Part 2 was determined with respect to the comparison of the combined “Booster” (i.e., fixed-time and on-demand) groups *vs*. the control group. Including 105 participants allows to estimate a difference in the AUPC of 45 between the “Booster” groups and the control group and a difference of the AUPC of 51 between the fixed-time and on demand group with a power of 80%.We assume a standard deviation of 76 for the AUPC in all groups, which corresponds to a Cohen’s d of 0.6. Calculations were done assuming a two-sided alpha of 5% and using a two-sample *t*-test for comparison.

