#### 2.9.3 Sensitivity analyses

In order to further examine the effect of OLP application on subjective pain ratings, the following sensitivity analyses will be conducted:

1.In order to be able to directly compare the results with previous studies (55), we will repeat the primary analysis for a restricted AUPC using only the first 90 min of measurement.2.We will explore the relationship between the outcome and the time between the two visits by fitting a linear regression model with the difference in the AUPC as the outcome and the arm, the time between the visits and the interaction term arm × time between visits as predictors.3.We will examine the relationship between the difference in the AUPC and several demographic covariates namely (i) age (ii) sex, and (iii) level of education. To this end, we will fit linear regression models with the difference in the AUPC as the outcome and the arm, the covariate and the interaction term arm × covariate as predictors.

These sensitivity analyses are exploratory and not confirmatory, hence no hypotheses are tested and *p*-values will be interpreted as continuous measures that inform the generation of new hypotheses worthy of further investigation.

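### Part 2 balances gender at recruitment and records sex, but no Part 2 analysis as written uses it; adding sex to the AUPC comparison is a cheap, modest gain in precision

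*Protocol article*

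**What the plan says.** - **Recruitment (2.4.1):** "A balanced gender distribution will be ensured during recruitment". No quota per group is given.
- **Allocation (2.4.3):** "For Part 2, group allocation will be randomized" to control, fixed-time booster or on-demand booster. The method is given as "Randomization will be performed by study staff not involved in study assessments using a random number generator". No ratio, block or stratum is described, and none is ruled out.
- **Size (2.3, 2.8):** 105 participants in Part 2, with an SD of 76 in every group. "Including 105 participants allows to estimate a difference in the AUPC of 45" for combined boosters against control, and "a difference of the AUPC of 51 between the fixed-time and on demand group with a power of 80" (per cent).
- **Part 2 primary analysis (2.9.1):** a two-sample t-test of combined boosters against control and then, if that is significant, a two-sample t-test of fixed-time against on-demand. Neither includes a covariate.
- **Sex in the analysis (2.9.3):** sex is listed with age and education in an exploratory analysis, where "we will fit linear regression models with the difference in the AUPC as the outcome and the arm, the covariate and the interaction term" are the ingredients.

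**The concern.** The sponsor takes the trouble to balance gender among those recruited and lists sex as a covariate worth examining, so it will be on file for every participant. The Part 2 question, however, is answered between groups of about 35, and balance in the total does not carry over to the groups unless the allocation list or the analysis makes it do so.

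The analysis as written does not. The model in 2.9.3 needs one difference in AUPC per person. Section 2.9.2 spells out the corresponding quantity for the other variables of interest as intervention visit minus control visit. That exists in Part 1, where each participant has two visits. Part 2 has one visit per participant (2.4.2), so the outcome of this model is undefined there.

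At stake is precision: any variation in AUPC due to sex stays in the error term, and a chance difference in sex mix stays in the estimate of the one trial that is run. Planned power is close to 80% with little to spare, so a nearly free improvement is worth having.

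**Working it through.** **Inputs from the article.** N = 105, SD = 76, differences of 45 and 51, two-sided 5% (2.3, 2.8).

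**Assumptions.** 1:1:1 allocation, so 35 per group and 70 against 35 for the first contrast; 53/52 by sex; a sex difference δ of 15 to 45 AUPC units. The article gives no sex effect. If AUPC is in NRS points × minutes over 180 min, this range is 15/180 = 0.08 to 45/180 = 0.25 NRS points on average.

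**1. The plan's own figure.**
- Boosters vs control: SE = 76 × √(1/35 + 1/70) = 15.7; 45/15.7 = 2.86; normal-approximation power 81.6%, noncentral t 80.9%.
- Fixed-time vs on-demand: SE = 76 × √(2/35) = 18.2; 51/18.2 = 2.81; power 80.2%, noncentral t 79.0%.

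The stated 105 reproduces: the first contrast needs 34 controls (102 in total) and the second needs 35 per group (105).

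**2. How often sex mix differs by chance.** Simulation of 400,000 allocations, simple 1:1:1:

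| Gap in sex share | Fixed-time vs on-demand | Boosters vs control |
|---|---|---|
| 15 points or more | 22% | 15% |
| 20 points or more | 10% | 5% |

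With group sizes fixed at 35 but no sex strata, the 20-point figures are 12% and 6%. With sex-stratified permuted blocks the largest gap between any two groups was 2.9 points (blocks of 3) or 4.4 points (blocks of 6).

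**3. What a gap does to the estimate.** Shift = gap × δ. At 20 points: 0.20 × 15 = 3 and 0.20 × 45 = 9 units. That is 3/45 = 7% to 9/45 = 20% of the planned difference of 45, or 0.2 to 0.6 of the SE of 15.7.

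**4. What adjusting gains.** If 76 is the SD across both sexes, an equal mix contributes δ²/4 to the variance, so residual SD = √(76² − δ²/4):

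| δ | Residual SD | Power, boosters vs control | Power, fixed-time vs on-demand |
|---|---|---|---|
| none | 76.0 | 80.9% | 79.0% |
| 15 | 75.6 | 81.3% | 79.4% |
| 45 | 72.6 | 84.3% | 82.6% |

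The gain is 0.4 to about 3.5 points. The degree of freedom itself costs about 0.01 to 0.02 points. The table takes the groups as nearly balanced on sex. Without strata, the adjusted variance is inflated by 1/(1 − r²), where r is the correlation of sex with the contrast and r² averages about 1/104 = 1%. At δ = 15, sex explains 15²/4 ÷ 76² = 1% of the variance, so the net gain there is about nil.

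**The case against.** **Allocation may well be stratified.** A random number generator can produce a blocked, stratified list, and a condensed article commonly leaves such detail to the full protocol. This stands. A reader might infer from 2.4.3 that randomisation is unstratified; the text does not say so, and the imbalance figures above are conditional on simple allocation. The analysis point does not depend on it: if the list is stratified by sex, a t-test that ignores the stratum still leaves the sex variation in the error term.

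**Chance imbalance is not bias.** This also stands. The t-test keeps its 5% error rate, and variation due to sex is already inside the SD of 76 used for power. The plan is valid as written.

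**The current is titrated.** Section 2.4.2.2 adjusts it for each person towards the same pain rating before the first injection. That should narrow sex differences in pain at the start of the measured period and argues for the lower part of the assumed range. It does not rule out differences in habituation or placebo response later.

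**Perhaps 2.9.3 is meant to use plain AUPC in Part 2.** Possibly, but it would need to say so, and it would still be an exploratory interaction model, separate from the primary comparison.

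**Nothing is contradicted.** True: no sentence promises balance within groups, and balanced recruitment may simply serve representativeness.

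**Conclusion.** The point holds for Part 2 as a modest, low-cost improvement. Sex is balanced at recruitment and recorded, yet the Part 2 primary tests ignore it and the one model that contains it cannot be fitted to Part 2 data as defined. On the assumptions of 1:1:1 allocation and a sex difference of 15 to 45 units, adjusting is worth roughly 0.4 to 3.5 points of power, and it removes a chance shift of 3 to 9 units in the minority of trials where the gap reaches 20 points.

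Two stronger readings are not supported:
- A reader might assume a sex difference of one NRS point over 180 min, which at a 20-point gap shifts the contrast by 0.20 × 180 = 36 units, close to the planned 45. But with an equal mix a 180-unit difference alone implies an SD of 180/2 = 90, above the planned 76 for all variation together.
- A reader might extend the point to Part 1. There each participant is their own control and the estimator allows for period effects, so a sex difference in pain level cancels. Only a sex-by-period effect could remain, and the article gives no figure for one.

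**What to change.** In 2.9.1, replace the two Part 2 t-tests with a linear model of AUPC on group (three levels) and sex. Keep the same two contrasts in the same order: the average of the two booster groups against control, then, only if that is significant, fixed-time against on-demand. In 2.9.3, state the outcome of the covariate models for Part 2 (AUPC itself) or confine those models to Part 1.

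The cost is one model term and one degree of freedom, with no added participants, visits or data. The change should be fixed before Part 2 outcomes are examined by group.

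Optional: if the full protocol does not already stratify, use sex-stratified permuted blocks for participants not yet randomised and leave existing allocations as they are. This also avoids the small variance inflation noted above. If stratification is already in place, one sentence in 2.4.3 saying so is enough.
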